## Abstract

**Background:**

Supporting young employees as they navigate the changing workplace requires focus on personal resources. Although self-efficacy is a key and malleable resource, its context specificity limits its applicability. To address this, we propose to target meta self-efficacy, a construct reflecting an individual’s ability to leverage self-efficacy sources (mastery experiences, vicarious experiences, persuasion, and affective and physiological states) to build self-efficacy specific to any challenge and, in turn, safeguard their occupational health.

**Objective:**

The goal of this study is to co-create (co-creation phase) and verify the efficacy (randomized controlled trial [RCT] phase) of an internet intervention enhancing meta self-efficacy to support the occupational health of young employees.

**Methods:**

The co-creation phase will be based on the participatory approach principle and comprise 4 focus groups, where a total of 24 participants will contribute to meta self-efficacy–enhancing activities and identify needs for the intervention format. After each focus group, a preliminary qualitative analysis will be conducted, and the intervention draft will be refined. To detect an effect size of *d*=0.25, the RCT will use a 2-arm parallel design with a total sample size of 600 comparing the meta self-efficacy intervention against a placebo. Assessments will be conducted at the posttest time point and 3- and 6-month follow-ups, with work self-efficacy as the primary outcome and job stress, job affective well-being, and work capabilities as secondary outcomes, as well as meta self-efficacy as the manipulation check*.* Data will be analyzed using linear mixed-effects models following the intention-to-treat approach. The trial will also examine the impact of adherence and engagement on intervention outcomes and compare treatment credibility.

**Results:**

As of November 20, 2025, a total of 24 participants have been recruited, with 3 of 4 focus groups conducted and the final one to be completed by the end of 2025. RCT recruitment is scheduled to start at the beginning of 2026, with the last follow-up expected by the end of 2026.

**Conclusions:**

In comparison to the placebo control, we expect the intervention to significantly improve young employees’ work self-efficacy (primary outcome) and occupational well-being (secondary outcomes). If effective, the meta self-efficacy–enhancing intervention could bolster the ability to cope with various challenges in the health domain and beyond, extending the effect beyond the initial occupational context.

**Trial Registration:**

ClinicalTrials.gov NCT06944990; https://clinicaltrials.gov/study/NCT06944990

**International Registered Report Identifier (IRRID):**

PRR1-10.2196/85082

## Introduction

### Background

Early adulthood, spanning the ages of 18 to 30 years, is a critical period for establishing long-term psychological health, coinciding with the onset of major mental health disorders [1]. A central source of stress during this stage is the transition to independent living and professional life [2]. Work-related stress is particularly significant as it can affect the health of young adults and have long-term implications for employability, with research showing that young employees are seemingly more vulnerable to burnout than older workers [3].

Systematic reviews indicate that young employees face numerous job demands that can adversely affect their mental health [4,5]. Meanwhile, global trends are introducing a host of new workplace stressors—ranging from subtle disruptions such as inadequate technology or work interruptions [6] to serious challenges such as economic inequality, increasingly demanding work conditions [7], or uncertainty about work in light of artificial intelligence [8]. Young employees entering the workforce today will need to navigate these evolving challenges throughout their careers.

While organizations hold the primary responsibility for mitigating job demands and safeguarding employees’ health and well-being, such efforts can be slow in adapting to evolving challenges [9]. Thus, young employees may benefit from simultaneously building their own resources to cope with an increasingly unpredictable work environment. According to the conservation of resources theory [10], while resource loss causes stress, gaining resources protects individuals from stress and facilitates further resource accumulation—a process known as a *gain spiral*. Thus, consistent with the conservation of resources theory, developing psychological resources should help mitigate stress and generate additional benefits. In particular, strengthening young employees’ psychological resources should also support long-term well-being and enhance sustainable employability, defined as maintaining health and productivity over the course of one’s career [11]. To contribute to this goal, we propose to investigate enhancing a psychological resource that has the potential to foster long-term coping in changing circumstances: *meta self-efficacy*.

Bandura [12] defines self-efficacy as “beliefs in one’s capabilities to organize and execute the courses of action required to manage prospective situations.” It is considered a key personal resource [13] that can be deliberately improved through interventions due to its 2 main characteristics. First, self-efficacy is derived from 4 sources: mastery experiences, vicarious experiences, persuasion, and affective and physiological states [12]. Interventions designed to enhance self-efficacy usually incorporate activities based on these sources. Second, self-efficacy is context specific, meaning that it applies to particular tasks or domains. Context-specific self-efficacy has been tested in the health domain, facilitating processes such as habit modification or managing stress and burnout at work [14,15]. However, a limitation of context-specific self-efficacy interventions is that they can only strengthen self-efficacy within a narrowly defined domain. Participants in such interventions engage in a fixed number of activities enhancing self-efficacy in a particular setting. However, as a result, they do not necessarily internalize the root mechanism of self-efficacy. What is needed is the ability to intentionally recognize and leverage the sources of self-efficacy regardless of the challenges at hand, which might prove crucial for coping with life difficulties that are unexpected, fluctuating, and extend beyond the scope of a single intervention.

To address this gap, we propose the concept of meta self-efficacy, defined as “one’s ability to actively recognize, adapt, and leverage the 4 sources of self-efficacy beliefs in various contexts, as needed.” Because meta self-efficacy encompasses tapping into self-efficacy sources and considers the very mechanism of self-efficacy development, it is distinct from context-specific self-efficacy, which pertains to perceived capabilities in particular domains. Meta self-efficacy also differs from general self-efficacy. General self-efficacy reflects global positive self-beliefs about one’s abilities [16,17], whereas meta self-efficacy is an actionable skill and can be viewed as a context-free personal resource. In a separate study, we introduced the concept of meta self-efficacy and validated a questionnaire designed to measure it, examining both its internal and external validity [18]. In the context of an intervention, enhancing meta self-efficacy would enable individuals to intentionally leverage situations that may constitute sources of self-efficacy, such as experiencing gradual success with a specific task despite obstacles, to deliberately build the self-efficacy required for a specific task or domain. Consequently, an intervention aimed at enhancing meta self-efficacy would bolster a broad and transferable resource rather than one limited to the context of a single challenge.

### Study Aims

The overarching research question of this study is whether enhancing meta self-efficacy via an intervention can improve work self-efficacy and multidimensional occupational well-being in young employees. To address it, we will conduct a 2-phase investigation involving an intervention co-creation study and a randomized controlled trial (RCT).

In the co-creation phase, we will conduct a qualitative study to co-design the meta self-efficacy intervention in collaboration with its intended end users, young employees. This program will be delivered in the format of an internet intervention [19]. While internet interventions, including those targeting self-efficacy, have been successfully delivered [15,20], they often face challenges with adherence, engagement, and retention, particularly when they are self-administered [21,22]. To mitigate these risks, the co-creation phase will use a participatory design to develop meta self-efficacy activities based on the lived experiences of young employees and tailor the intervention format to their specific preferences. This phase is expected to improve the intervention’s general quality and, in turn, support adherence and engagement [23].

In the RCT phase, we will test the intervention’s efficacy comparing the meta self-efficacy intervention to a placebo. The goal is to assess the basic effect that the meta self-efficacy intervention can produce while controlling for the expectation bias [24]. We will additionally compare treatment credibility between conditions. Although meta self-efficacy is potentially applicable universally across life domains, testing its enhancement within the framework of the theory by Bandura requires concentrating on a specific background. In particular, enhancing meta self-efficacy should, in principle, lead to improvements in domain-specific self-efficacy. In this study, we test the effects of improving meta self-efficacy in the occupational context and among young employees, expecting that enhancing meta self-efficacy will improve their work self-efficacy (primary outcome). Furthermore, strengthening meta self-efficacy should lead to further well-being benefits [10], which we will measure as multiple dimensions of occupational well-being. These will reflect job-related emotions, stress levels, and work capabilities, encompassing behaviors and values. Accordingly, the secondary outcomes include job stress [25], job affective well-being [26], and work capabilities [27]. We expect improvements in both primary and secondary outcomes immediately after the intervention, with effects sustained at follow-ups. Additionally, a secondary objective of the RCT phase is to examine how factors such as intervention engagement and adherence relate to the intervention’s efficacy.

## Methods

### Ethical Considerations

This study has been approved by the ethics committee of the Institute of Psychology at SWPS University in Warsaw, Poland (opinion 11/2025). We will obtain informed consent from all study participants. Participants in the co-creation phase will receive a reimbursement in the form of online gift cards (€25; US $29.30) per 1.5-hour session, whereas participants in the RCT phase will not be reimbursed. Focus groups will be audio recorded and transcribed. Transcripts will be anonymized, and the original recordings will be deleted afterward. In the RCT phase, data collected via online surveys will be analyzed in anonymized form. The content of participant-generated data within the intervention will not be analyzed. Adherence will be assessed automatically using use data, which will also be analyzed in anonymized form.

### Registration

The RCT has been preregistered on ClinicalTrials.gov (NCT06944990). Protocol reviews from the grant application stage are available in Multimedia Appendix 1. Any deviations from the protocol will be documented in future reports of the study results. The RCT protocol follows the SPIRIT (Standard Protocol Items: Recommendations for Interventional Trials) guidelines [28], with the checklist available in Multimedia Appendix 2.

### Co-Creation Phase

#### Design

During the co-creation phase, we will conduct 4 focus groups. The first 2 groups (independent samples) will predominantly explore experiences with occupational well-being, centering on meta self-efficacy. The goal is to assess relevant behaviors and strategies connected to leveraging self-efficacy sources to create intervention activities, ensuring that the intervention’s content is relevant. In contrast, the third and fourth focus groups, comprising a new sample of participants taking part in 2 meetings, will focus on refining a prototype version of the activities already incorporated into a technological solution for the intervention. In these sessions, participants will review a preliminary version of the meta self-efficacy intervention activities and provide targeted feedback to further refine its content, design, and functionality.

#### Sample

The co-creation phase will be conducted among young employees, the same population targeted in the subsequent RCT phase. To participate in the focus groups, individuals must meet the following inclusion criteria: (1) be aged between 18 and 30 years and (2) have been professionally active for at least the 2 previous months, working at least part time or a minimum of 20 hours per week. Focus groups will be conducted on 3 samples of 8 participants for a total of 24 unique participants, with one sample taking part in 2 sessions. Consistent with qualitative research practices, our focus group sample size aligns with recommendations for achieving data saturation and capturing rich, in-depth insights. Vasileiou et al [29] note that qualitative studies often rely on small, purposively selected samples—with saturation frequently reached with as few as 6 to 8 participants per group. Accordingly, using 3 samples for a total of 4 focus groups (N=24) is appropriate for the exploratory co-creation phase as it prioritizes data adequacy over statistical generalizability.

#### Procedure

Potential participants will be recruited through multiple channels, including advertisements, personal contacts, and a university credit exchange system. Advertisements with a brief description of the participation terms will be disseminated as digital posts via social media platforms (eg, Facebook). The university credit exchange system is an internal online platform through which students can sign up to participate in research projects in return for gift cards or study credits that can be used to fulfill course requirements. In this study, this platform will serve solely as a recruitment channel to reach young employees, and all focus group participants will receive the same reimbursement. Those who are interested, meet the inclusion criteria, and consent to participate via an online recruitment form will be invited to one of the in-person focus groups. Each session will last approximately 1.5 hours, although the duration might vary. Participants will be reimbursed for their effort with online gift cards (valued at approximately €25; US $29.30) per 1.5-hour participation.

#### Qualitative Data Collection

The 4 focus groups will follow a semistructured format combining predetermined questions with open discussions. This approach ensures that, while participants respond to set questions, they are still encouraged to elaborate on and engage in a dialogue, allowing for a structured inquiry while also capturing diverse perspectives.

The first 2 focus groups (separate samples, n=8 each) will begin by exploring young employees’ experiences with occupational well-being, with a main focus on meta self-efficacy. Discussions will cover four key topics: (1) sources of occupational stress and well-being; (2) distinctions among specific, general, and meta self-efficacy beliefs; (3) behaviors and strategies for leveraging self-efficacy sources; and (4) potential ways to enhance meta self-efficacy and initial requirements for an internet intervention. Subsequently, within the research team, we will discuss the findings and compile a list of the most salient meta self-efficacy strategies, integrating them with proposed activities and the predetermined components of the intervention (see the Meta Self-Efficacy Intervention and Analysis sections). We will prepare an initial version of the intervention based on this. In the third focus group, a new sample of participants (n=8) will review the content and format of the initial version of the meta self-efficacy intervention. Discussions will include (1) occupational well-being, as well as specific, general, and meta self-efficacy to introduce participants to the scope of the intervention; (2) opinions on the psychological content of the activities, with a focus on meta self-efficacy strategies; and (3) technological aspects, such as visuals, user experience, notifications, and others. During the fourth and final focus group, we will present a refined version of the intervention to the same participants. They will be asked to provide areas for potential improvements and remaining concerns regarding both the content of the activities and the intervention format. Figure 1 illustrates the process of collecting qualitative data alongside the iterative refinements made to the meta self-efficacy intervention. The topic guide for the focus groups is provided in Multimedia Appendix 3.

**Figure 1 figure1:**
[figure not shown]
Qualitative data collection and iterative intervention refinements.

The co-creation phase will be conducted in person and moderated by a psychologist. Focus group discussions will be audio recorded and later transcribed for analysis. Participants’ privacy will be respected, and we will inform them about the recordings during recruitment and again before the focus group sessions begin.

#### Analysis

A preliminary qualitative analysis of each focus group will inform the iterative development of the meta self-efficacy internet intervention (Figure 1). First, transcripts from focus groups 1 and 2 will be assessed to identify user requirements and preferred features, as well as to compile a catalog of meta self-efficacy strategies. Second, the research team will discuss these findings and incorporate the proposed meta self-efficacy strategies into the theoretical model of the intervention (see the Meta Self-Efficacy subsection) based on the framework by Bandura [16]. Draft intervention scripts and delivery format screenshots will then be created. Third, this initial version of the intervention will be discussed in focus group 3 to gather participants’ opinions, elicit suggestions for improvement, and identify additional meta self-efficacy strategies. Fourth, after further refinement of the intervention contents and technological aspects of the delivery modality, a revised iteration will be presented in focus group 4. Feedback from this session will focus on fine-tuning the content and format of the activities to finalize the intervention before the RCT begins.

After the study is completed, we will conduct an additional analysis to identify the barriers and facilitators that emerged during the iterative intervention development. We will then carry out an in-depth thematic analysis to address the following research question: “What aspects facilitate or hinder uptake and engagement in the meta self-efficacy intervention?” We will analyze all focus groups collectively, tracking what facilitators and barriers emerge throughout the intervention’s iterative development. Following the principles of reflective thematic analysis [30], the process will unfold in 6 stages. First, the project’s principal investigator will listen to the recordings and review the transcripts to familiarize himself with the data to generate initial codes by identifying transcript sections relevant to the research questions. In the third step, the principal investigator will group codes into themes representing specific meanings. In the 2 subsequent stages, the research team will iteratively review and name the themes. In the final step, we will refine the themes into a coherent narrative and prepare the final write-up.

### RCT Phase

#### Study Design

To evaluate the efficacy of the meta self-efficacy intervention, we will conduct a 2-arm RCT. Participants will be randomly assigned (1:1) to 1 of 2 conditions: an experimental group with access to the meta self-efficacy–enhancing internet intervention or a placebo control group with access to educational content. A placebo comparator in the form of interactive educational content on occupational well-being has been chosen over a waitlist control [31] to avoid a typical expectation bias: participants in the intervention group usually expect improvement, whereas those on the waitlist do not. An active but nontherapeutic comparator delivered through the same modality as the intervention [24] will allow us to isolate the specific effect of the meta self-efficacy intervention while holding expectations similar in both groups. Outcomes will be measured at 4 time points: baseline, posttest, and 3- and 6-month follow-ups.

#### Sample

The trial will be conducted with a sample of young employees aged 18 to 30 years, representing the early adulthood life stage [2]. To participate in the RCT, individuals must meet the following inclusion criteria: (1) age between 18 and 30 years, (2) professional activity for at least 2 months before trial recruitment (minimum part-time employment or 20 hours per week), and (3) completion of the baseline assessment. Individuals who participated in the co-creation phase focus groups will not be eligible to participate in the RCT phase due to prior exposure to the intervention content and concepts.

#### Power Analysis

To determine the required sample size, we considered the effect sizes reported for internet interventions aimed at enhancing context-specific self-efficacy. These interventions have shown effect sizes of approximately *d*=0.5 for various stress-related outcomes [20,32]. However, the effect size for the meta self-efficacy intervention may differ and is likely smaller as it shifts the focus from enhancing self-efficacy in a specific context to bolstering the ability to leverage self-efficacy sources. To account for this, the trial is powered to detect a minimum meaningful effect of *d*=0.25. We conducted an a priori power analysis for a linear mixed-effects model using the *powerlmm* R package (R Foundation for Statistical Computing) [33]. Given 4 measurement points, an error level of α=.05, and power of 1 – β of 0.90, the analysis indicates that 600 participants are needed. This calculation factors in a 30% dropout rate based on a previous self-efficacy internet intervention for young adults and a broader review of adherence in mobile interventions [21,34].

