#### Statistical Analyses

##### Preliminary Analyses

We will conduct preliminary analyses, including a randomization check and dropout analysis, using ANOVAs and chi-square tests, as well as examine differential attrition through 2-tailed *t* tests. Dropout will be operationalized as attrition to posttest. Additionally, we will assess intervention-related adherence and engagement metrics (see the Other Metrics subsection).

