##### Intervention Efficacy

The intervention’s efficacy will be evaluated for each outcome measure following the intention-to-treat principle, meaning that all randomized participants will be included in the final analysis. The primary efficacy analysis will use a linear mixed-effects model, with a random intercept for participants and fixed effects of time and condition [42]. Although the expected dropout rate is included in our a priori power analysis, we will also examine the actual dropout rate and its characteristics. This examination will determine whether there is a significant difference in dropout percentages between the 2 conditions, a phenomenon known as differential dropout [43]. Subsequently, we will apply an appropriate missing data imputation method and calculate pooled results using linear mixed-effects models (eg, using the *mice* and *mitml* R packages [44]). Sensitivity analyses will be conducted to examine the robustness of the results and compare intervention effect estimates across per-protocol, intention-to-treat, and imputed data analyses. Additionally, we will verify the credibility of the placebo in comparison to the intervention condition.

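### The stated 90% power for d=0.25 with 600 participants does not belong to the primary model as written, and the visit to which the 30% dropout applies is not stated

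*Protocol article*

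**What the plan says.** The Power Analysis section states that "the trial is powered to detect a minimum meaningful effect of *d*=0.25", with "an error level of α=.05" and power 0.90, for a linear mixed-effects model run in a named R package. It starts from "Given 4 measurement points", concludes that "the analysis indicates that 600 participants are needed", and adds: "This calculation factors in a 30% dropout rate". It does not name the coefficient tested, the within-person correlation, the visit at which d applies, or the visit by which 30% are lost.

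Intervention Efficacy gives the only primary model: "The primary efficacy analysis will use a linear mixed-effects model, with a random intercept for participants and fixed effects of time and condition". No interaction is mentioned there or elsewhere.

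Preliminary Analyses contains the only definition of dropout: "Dropout will be operationalized as attrition to posttest".

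Three further facts matter. Under Procedure, participants complete baseline (T1) and are then randomized. Under Outcome Measures, every outcome is assessed at all time points. Under Study Aims, the effect is expected at posttest (T2) and should persist at 3 and 6 months (T3, T4).

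**The concern.** Randomization after T1 makes the arms equal in expectation at baseline. A model with time and condition but no interaction fits one constant arm difference across T1-T4, so the treatment effect is averaged with a zero. That model tests something smaller than d=0.25, and the power for 0.25 does not carry over to it.

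The second issue is the 30%. The calculation counts four visits, while the article's only definition of dropout stops at T2. If that definition also underlies the 30%, loss between T2 and T4 is outside the calculation. Trial participants are not reimbursed (Ethical Considerations), and the Discussion itself treats attrition as a risk, so further loss is plausible.

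At stake is the reading of a null result: it would be reported as coming from a trial with 90% power for the smallest effect of interest when the analysis actually run may have had much less.

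**Working it through.** **Inputs.** From the article: N=600, 1:1 allocation, d=0.25, alpha 0.05, four visits, 30% dropout. Assumed, because the article is silent: two-sided test; total variance 1; one common within-person correlation ρ (the random-intercept structure), varied from 0.2 to 0.8; equal arms at T1 and a difference of 0.25 at T2-T4; monotone dropout, the same in both arms; normal approximation.

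**Step 1. Can 600 be reproduced?** Not uniquely. It is reached with a linear time-by-condition slope (0.25 at T4) at ρ about 0.62 (30% lost by T4) or 0.63 (30% lost by T2), with a categorical time-by-condition contrast at ρ about 0.59-0.67, and with a baseline-adjusted T2 comparison at ρ about 0.61-0.62. The article does not show which setting was used.

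**Step 2. The model as written.** Let p_k be the share of participants observed at exactly the first k visits.

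- Information: W = Σ p_k · k / (1 + (k−1)ρ)
- Signal: S = Σ p_k · 0.25(k−1) / (1 + (k−1)ρ)
- Expected condition coefficient = S / W; SE = √(4 / (600·W)); power = Φ(coefficient/SE − 1.96)

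With no dropout the coefficient is 0.25 × 3/4 = 0.1875. At ρ=0.5, W = 4/2.5 = 1.6, SE = √(4/960) = 0.0645, and power = Φ(2.905 − 1.96) = 0.83, already below 0.90.

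With 30% lost by T2 (p₁=0.3, p₄=0.7) at ρ=0.5:

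- W = 0.3 + 0.7 × 1.6 = 1.42
- S = 0.7 × 0.75/2.5 = 0.21
- Coefficient = 0.21/1.42 = 0.148; SE = √(4/852) = 0.0685
- Power = Φ(2.16 − 1.96) = 0.58

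The same formulas give:

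| ρ | 30% lost by T2 | 30% lost evenly by T4 | 30% lost only at T4 |
|---|---|---|---|
| 0.2 | 0.80 | 0.88 | 0.93 |
| 0.3 | 0.72 | 0.82 | 0.89 |
| 0.4 | 0.64 | 0.77 | 0.84 |
| 0.5 | 0.58 | 0.71 | 0.80 |
| 0.6 | 0.52 | 0.66 | 0.75 |
| 0.7 | 0.47 | 0.61 | 0.71 |
| 0.8 | 0.43 | 0.57 | 0.67 |

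The coefficient lies between about 0.14 and 0.18 throughout. In this range power passes 0.90 only at ρ=0.2 with all loss at T4. Below 0.2 the other patterns can pass it too (at ρ=0.05: 0.92 with loss by T2, 0.96 with even loss).

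**Step 3. If a time-by-condition contrast is intended.** Take the T2 difference with baseline constrained equal and 30% lost by T2, so 600 × 0.7 = 420, or 210 per arm.

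- SE = √(2(1−ρ²)/210); power = Φ(0.25/SE − 1.96)
- ρ=0.5: SE = √(1.5/210) = 0.0845, power 0.84
- ρ=0.6: power 0.89; ρ=0.7: power 0.95
- 0.90 requires SE = 0.25/(1.960+1.282) = 0.0771, so 1−ρ² = 105 × 0.0771² = 0.624 and ρ = 0.61

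**Step 4. Loss after T2.** Suppose, purely as an illustration, 30%, 40% and 50% are lost by T2, T3 and T4. At T4, 150 per arm remain. At ρ=0.5, completers alone give SE = √(1.5/150) = 0.100 and power Φ(2.5 − 1.96) = 0.71. The baseline-constrained mixed model, which also uses T2 and T3 data from those who leave later, gives about 0.72. The T2 contrast stays at 0.84, because these later losses do not touch it.

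**The case against.** The strongest reply is that 600 has not been shown to be wrong. A condensed article may write time and condition as shorthand for a model with their interaction, and Study Aims fits that reading. The figure is then attainable at correlations near 0.6. This stands: a reader might infer an arithmetic error in 600, and the article does not support that, since it gives no correlation to contradict.

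Second, the article does not say what d=0.25 refers to. If it is the condition coefficient itself, the written model with 30% lost by T2 has power 0.99 down to 0.90 over ρ 0.2 to 0.8. That is correct as arithmetic. But with arms equal at baseline, a coefficient of 0.25 requires a larger difference after baseline: at ρ=0.5, 0.25 × 0.25/0.148 = 0.42. That would no longer be power for a difference of 0.25 at the visits where the treatment can act.

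Third, no section says that the 30% is loss to posttest only. The definition sits under Preliminary Analyses and governs the dropout analysis; the 30% might equally be loss by T4. This also stands, and the point about later loss is therefore conditional.

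Fourth, a plain two-sample calculation (674 participants, or 674/0.7 = 963 with dropout) might look like proof of a shortfall. It is not the stated method and carries no weight here.

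Finally, unreported inputs are normally left to a fuller document. That answers a complaint about missing detail alone. It does not answer a mismatch between a power figure and a primary model that the article itself states.

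**Conclusion.** The concern holds as a mismatch between the stated power and the stated model. Followed literally, the primary model does not deliver 0.90 for a post-baseline difference of 0.25: power is about 0.80-0.43 with 30% lost by T2 and 0.88-0.57 with even loss by T4, over ρ 0.2-0.8. The exception in that range is ρ=0.2 with all loss at T4, so a claim that 0.90 fails under every setting would be too strong.

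If an interaction contrast is meant, 600 may be right, but with 30% lost by T2 it depends on an undisclosed correlation of roughly 0.6 or more. The visit attached to the 30% is unstated. Only if it means loss to posttest is later loss uncovered, and then power at T4, not at T2, suffers. The correlations, the loss patterns and the 50% loss by T4 are assumptions of this check, not figures from the article. The article should resolve this, but it does not call for a larger trial.

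**What to change.** Keep N=600 and make these changes:

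- Put the time-by-condition term, or a baseline-constrained equivalent, in the primary model.
- Name the contrast that tests work self-efficacy and its time point.
- Say what d=0.25 refers to and at which visit.
- State the assumed within-person correlation and the expected dropout at T2, T3 and T4, and make clear whether the 30% is loss to posttest or to 6 months.
- Rerun the power for that contrast and give T3 and T4 power separately. If T2 is chosen, the statement could read: power 84% to 95% for correlations of 0.5 to 0.7 with 30% lost by T2.

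The cost is a text revision and one rerun, with no extra participants. The downside is that the restated power may be less favourable than 90%, particularly at the later visits.
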